## Abstract

**Background:**

Drug resistance in China is becoming a more and more serious issue. Infection by drug-resistant bacteria has become a major disease that seriously threatens the health of Chinese people and affects national medical finance. Therefore, it is of great scientific and clinical significance to actively carry out research on the prevention and treatment of infections by multi-drug resistant organisms (MDRO). Previous studies by the authors suggested that patients with hospital-acquired pneumonia caused by MDRO mostly showed the pathological state of “insufficient healthy *Qi* and internal accumulation of pathogenic *Qi*” and “acute deficiency syndrome” mainly characterized by *Qi* deficiency. *Buzhong Yiqi* decoction is a famous classic prescription in traditional Chinese medicine (TCM) for treating internal damage fever. This study intends to provide an evidence-based rationale for *Buzhong Yiqi* decoction in treating MDRO hospital-acquired pneumonia by conducting a multi-center randomized controlled clinical study.

**Methods/design:**

This study is designed to be a multi-center randomized controlled study in which patients are assigned randomly into control (standard therapy) and trial (standard therapy plus *Buzhong Yiqi* decoction) groups. The patients will be selected from the emergency department and the ICU inpatient department of five study sites and will all be diagnosed with MDRO hospital-acquired pneumonia and meet the inclusion criteria. Forty patients are to be enrolled in each study site, resulting in a total of 200 patients in the study. The treatment course is 28 days.

**Discussion:**

In this study: (1) the theory of “acute *Qi* deficiency” in MDRO hospital-acquired pneumonia is put forward for the first time, and the basic theories of TCM are further improved; (2) a multi-center randomized controlled clinical study will be performed for the first time with *Buzhong Yiqi* decoction, the classic prescription for reinforcing healthy *Qi* and eliminating pathogenic *Qi*, providing a reliable evidence-based rationale for the treatment of MDRO pulmonary infection with TCM; (3) the clinical application and modern disease spectrum of *Buzhong Yiqi* decoction is expanded, and the scientific notion of “treating different diseases with the same method” is enriched further.

**Trial registration:**

China Clinical Trial Registry, ChiCTR1900022429. Registered on April 11, 2019. http://www.chictr.org.cn/listbycreater.aspx.

## Background

Clinical studies on hospital-acquired pneumonia (HAP) and/or ventilator-associated pneumonia (VAP) have detected multi-drug-resistant organisms (MDROs) in most respiratory secretions from patients in intensive care units (ICUs), with the isolation rate increasing year on year [1–4]. In recent years, the national bacterial resistance surveillance report has revealed that MDROs have, to varying degrees, serious epidemic characteristics in different provinces of China. The increasing social burden of MDRO infections arises from adverse clinical outcomes and aggravated economic and medical burdens [5–7].

HAP caused by MDRO infection is a common and major clinical disease, especially in emergency departments and ICUs [8]. According to its clinical manifestations, the disease can generally be classified as “pulmonary fever” in traditional Chinese medicine. Our previous clinical studies found that HAP caused by MDROs, due to the underlying and excessive pathogenic factors prevailing over the normal resistance of the body, first showed the signs of *Qi* deficiency, especially weakness of the spleen and stomach, giving rise to a pathological state of mainly “acute *Qi* deficiency”. Combining with theories from traditional Chinese medicine (TCM), we innovatively put forward a theory of “acute deficiency syndrome” in critical and severe cases of HAP caused by MDRO infection. Based on studies by other scholars on TCM syndrome types of MDRO HAP [9–12], we believe that the core pathogenesis of MDRO HAP is “insufficient healthy *Qi* and internal accumulation of pathogenic *Qi*”, in which “acute *Qi* deficiency syndrome” is critical.

*Buzhong Yiqi* decoction was proposed in *On Spleen and Stomach* by Li Dongyuan, one of the four greatest medical scientists in the Jin and Yuan Dynasties. It is a famous classical prescription in TCM and also a typical representative prescription in treating internal damage fever. According to TCM, “Pathogenic *Qi* cannot invade the body with sufficient healthy *Qi* inside” and disease occurs when healthy *Qi* is weak. Supplementing pectoral *Qi* is the method to cure the root cause, and abundance of pectoral *Qi* depends on the lung and spleen. Li’s *Buzhong Yiqi* decoction was formulated considering the methods of “treating impairment with supplementing” and “treating overstrain with warming” in *The Yellow Emperor’s Canon of Internal Medicine*, pioneering the school of “relieving great fever with drugs sweet in taste and warm in property”. This prescription consists of *Radix Astragali seu Hedysari*, *Radix Ginseng*, *Radix Glycyrrhiza*, *Rhizoma Atractylodis Macrocephalae*, *Radix Angelicae Sinensis*, *Pericarpium Citri Reticulatae*, *Rhizoma Cimicifugae*, and *Radix Bupleuri*. In the prescription, *Radix Astragali seu Hedysari* is the sovereign medicinal that invigorates *Qi*, *Radix Ginseng* is the minister medicinal that powerfully tonifies the primordial *Qi*, nourishes the lung, and invigorates the spleen, *Rhizoma Atractylodis Macrocephalae* invigorates the spleen, *Radix Angelicae Sinensis* regulates the blood, *Pericarpium Citri Reticulatae* regulates *Qi*, and prepared *Radix Glycyrrhiza* helps *Radix Ginseng* and *Radix Astragali seu Hedysari* rectify *Qi*; *Rhizoma Cimicifugae* and *Radix Bupleuri* have the function of eliminating pathogens and raising the clear yang. The whole formula supplements and clears in that it not only tonifies the middle and replenishes *Qi*, but also unblocks [13–16].

Clinical pharmacological studies with *Buzhong Yiqi* decoction have demonstrated that it enhances phagocytosis of the reticuloendothelial system, promotes the non-specific immune function of the body, and has a remarkable inhibitory effect on multi-drug-resistant *Staphylococcus aureus* [17, 18]. This recipe can effectively alleviate inflammatory reactions and boost immunity of the body. Results from previous studies by the authors on *Buzhong Yiqi* decoction for the treatment of HAP, including that caused by MDROs, showed that TCM could significantly relieve the inflammatory reactions of patients, improve clearance of the organisms, shorten the time of mechanical ventilation, and increase the success rate of weaning from the ventilator and had good clinical efficacy. Similar clinical efficacy was observed in other related studies on *Buzhong Yiqi* decoction for the treatment of HAP [19–22]. Therefore, on the basis of previous studies, this study intends to provide an evidence-based rationale and guidance for the clinical treatment of MDRO HAP, further elucidate the scientific notion of “treating different diseases with the same method”, and expand the modern disease spectrum of *Buzhong Yiqi* decoction by performing a multi-center randomized controlled clinical study with *Buzhong Yiqi* decoction (a classical formula for reinforcing healthy *Qi* and eliminating pathogenic *Qi*) in the treatment of MDRO HAP.

## Methods/design

### Objective

We propose a multi-center randomized controlled clinical study to demonstrate the efficacy and safety of *Buzhong Yiqi* decoction in the treatment of MDRO HAP and to explore the possible mechanism, provide a reliable evidence-based rationale for the treatment of MDRO pulmonary infection with TCM, further elucidate the scientific notion of “treating different diseases with the same method”, and expand the modern disease spectrum of *Buzhong Yiqi* decoction. We do this to open up new ideas and methods for MDRO prevention and treatment strategies and formulate TCM diagnosis and treatment regimens for pulmonary infections caused by MDROs in clinical practice.

### Design

This study is a multi-center randomized controlled study in which patients will be assigned randomly into control and trial groups. The patients will be selected from the emergency department and the ICU inpatient department of five study sites after being diagnosed with MDRO HAP and meeting the inclusion criteria. The flow chart of the study is shown in Fig. 1. The date of study initiation was July 1, 2018 and the date of study completion is June 30, 2021. The Standard Protocol Items: Recommendations for Interventional Trials (SPIRIT) Checklist can be found in Additional file 1.

**Fig. 1 Fig1:**
[figure not shown]
Flow chart of the study

### Participants

From July 1, 2018 to May 31, 2021, patients will be selected from those treated in the emergency department and the ICU inpatient department of the five study sites, namely Longhua Hospital Shanghai University of Traditional Chinese Medicine, Shanghai Integrated Traditional Chinese and Western Medicine Hospital, Shanghai Seventh People’s Hospital, Shanghai Baoshan Integrated Traditional Chinese and Western Medicine Hospital, and Shanghai Pudong New Area Public Interest Hospital. All patients are diagnosed with MDRO HAP and meet the inclusion criteria. Forty patients are to be enrolled in each study site, resulting in a total of 200 patients in the study.

### Inclusion criteria

The eligibility criteria are as follows: (1) patients meet the diagnostic criteria of Western medicine; (2) etiological diagnosis meets the MDRO criteria; (3) aged 40–85 years; (4) patients have signed the informed consent form; (5) Patients also meeting the following criteria as Exclusion criteria, withdrawal/trial discontinuation/drop-out criteria are included into observation.

### Exclusion criteria

The exclusion criteria are as follows: (1) severe primary or malignant disease of the heart, brain, liver, kidney, or other organs or systemic disease at an acute or progressive stage; (2) surgery within 2 months accompanied by surgical site infection; (3) patients who have been hospitalized less than 72 h or who die within 72 h of hospitalization; (4) psychiatric patients and pregnant women; (5) active tuberculosis; (6) a history of allergy to on-treatment drugs; (7) recent drug and alcohol abuse; (8) patients who receive no other antibiotics or fail to respond to other antibiotics within 3 months prior to the clinical trial.

### Withdrawal/trial discontinuation/drop-out criteria

The rejection and withdrawal criteria are: (1) not meeting the inclusion criteria of the study; (2) incomplete clinical data obtained after inclusion and it is impossible to perform further clinical statistical analyses; (3) subjects experience severe adverse events/reactions related to the treatment regimen and the investigator considers it necessary to withdraw them from the trial; (4) during the trial, the patient’s condition continues to deteriorate and dangerous events are likely to occur such that the investigator considers it necessary to withdraw them from the clinical trial; (5) non-specified combination of drugs, especially those that have a great impact on the observational drug and affect efficacy and safety assessment; (6) patients who withdraw during the trial at their own discretion—all patients who complete the informed consent form and are eligible to enter the trial at screening, no matter when and why they withdraw, are classified as drop-out cases as long as they do not complete the observational period specified in the protocol; (7) poor treatment compliance that affects determination of efficacy and safety.

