### Randomization and allocation

In each study site, patients with MDRO HAP that fulfill the inclusion criteria and do not meet any of the exclusion criteria are assigned to the trial group or control group according to the corresponding random numbers extracted in the order at visit. Each study site will enroll 40 patients for a total of 200 over the five study sites. A random number table generated using Statistical Analysis Software (SAS), version 9.2, using the randomization method, will be used to assign the participants in a ratio of 1:1, with 100 patients each in the trial group and control group. A researcher will generate the allocation sequence and enroll participants and the clinical researchers will assign participants to interventions. The clinical researchers at each center will provide packaged drugs to the participants according to the randomization number on the packaging; the code labeling will conform to the principles of GCP. The statistician will uncover the blinding as necessary.

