### Sample size

Considering that no previous studies have been conducted to calculate the sample size, and assuming that the withdrawal rate is less than 15% [23], we expect that 100 patients will be enrolled in each arm, and that the final sample size of each arm will be at least 85. The data we collect will be helpful to calculate the appropriate sample size in the future and provide reference for further large-scale research.

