### Statistical analysis

#### Data analysis

The Longhua Hospital Shanghai University of Traditional Chinese Medicine will be in charge of data management and statistical analysis in this study. Statistical analysts are not involved in clinical observation; they are responsible for statistical analysis of study data and timely delivery of statistical reports to the study director. Statistical analysis will be performed with SPSS 20.0 software. Measurement data are expressed as mean ± standard deviation. Normality test and homogeneity test of variance will be performed first. In case of normal distribution and homogeneity of variance, a *t*-test is performed, otherwise a non-parametric test is used. Count data are expressed as frequency constituent ratio (percentage) and *X*^*2*^ test is performed. *P* < 0.05 indicates statistical significance.

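### The withdrawal rules take randomised patients out of the trial for reasons that include treatment failure, and the sample-size text counts only those left, so the primary comparison may omit failures

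*Protocol article*

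**What the plan says.** The section on withdrawal, discontinuation and drop-out gives a single list of criteria for both rejection and withdrawal. Apart from ineligibility, they arise after entry:

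- criterion 2: "incomplete clinical data obtained after inclusion and it is impossible to perform further clinical statistical analyses";
- criterion 3: severe events or reactions related to the treatment regimen, where the investigator judges withdrawal necessary;
- criterion 4, on removal from the trial itself: "condition continues to deteriorate and dangerous events are likely to occur such that the investigator considers it necessary to withdraw them";
- criterion 5: non-specified co-medication, especially where it affects the assessment of efficacy and safety;
- criterion 6: withdrawal at the patient's own choice, with the rule that eligible, consented patients who withdraw before completing the observation period are drop-outs, whatever the time or reason;
- criterion 7: "poor treatment compliance that affects determination of efficacy and safety".

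The Sample size section says "we expect that 100 patients will be enrolled in each arm", works by "assuming that the withdrawal rate is less than 15" per cent, and concludes that "the final sample size of each arm will be at least 85". The Data analysis section names the t-test, a non-parametric alternative and the chi-square test. No section names an analysis set, says how a withdrawn patient is graded on the primary outcome, or says whether follow-up continues after withdrawal.

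**The concern.** Criterion 4 describes treatment failure. A pneumonia patient who keeps getting worse fits the lowest grade of the primary outcome, lack of efficacy, but the rule takes that patient out of the trial. Criteria 5 and 7 follow per-protocol logic, and criterion 2 ties removal directly to the statistical analysis. If those removed also leave the denominator, the response rate in each arm is computed on a group selected partly by outcome.

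Criteria 3 and 4 depend on the investigator's judgement. The control arm receives standard therapy with no placebo described, so that judgement may be made knowing the arm, and removal rates can then differ between arms. CPIS and APACHE II comparisons would lose the same patients. Patients withdrawn because they are deteriorating are plausibly at high risk of death, and could be missing from day-28 mortality if nobody follows them after withdrawal.

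**Working it through.** **Inputs from the protocol article.** 100 enrolled per arm; withdrawal below 15%; at least 85 per arm remaining (Sample size). Allocation: "will be used to assign the participants in a ratio of 1:1" (Randomization and allocation). Significance: P < "0.05 indicates statistical significance" (Data analysis), taken here as two-sided. No response rate, effect size or power is given.

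**The plan's own figure.** 100 × (1 − 0.15) = 85, and 85 / (1 − 0.15) = 100. It reproduces exactly. Up to 15 per arm, 30 of 200, may therefore leave. Because the plan assumes less than 15%, 15 is the upper limit and not a typical value.

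**Assumptions for the illustration.** The four-level grade is reduced to response yes/no. The true rate is 60% in both arms, so 60 of 100 respond in each. Arm A loses 15 patients and arm B loses 5. A fraction f of those removed are failures.

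Rate among those left, with d removed: (60 − (1 − f)d) / (100 − d).

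| f | Arm A (15 removed) | Arm B (5 removed) | Gap | Type I error |
|---|---|---|---|---|
| 0.40 (unrelated to outcome) | 51/85 = 60.0% | 57/95 = 60.0% | 0 | 5% |
| 0.50 | 52.5/85 = 61.8% | 57.5/95 = 60.5% | 1.2 points | near 5% |
| 2/3 | 55/85 = 64.7% | 58.3/95 = 61.4% | 3.3 points | about 7% |
| 1 | 60/85 = 70.6% | 60/95 = 63.2% | 7.4 points | about 18% |

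With all 100 per arm in the denominator and withdrawn failures counted as failures, the f = 1 row is 60% v 60%, a gap of 0.

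**Type I error in the last row** (normal approximation with expected counts):

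- pooled rate 120/180 = 0.667;
- standard error under the null = √(0.667 × 0.333 × (1/85 + 1/95)) = 0.0704;
- standard error with separate rates = √(0.706 × 0.294/85 + 0.632 × 0.368/95) = 0.0699;
- chance of a significant result favouring arm A = Φ((0.0743 − 1.96 × 0.0704) / 0.0699) = Φ(−0.91) = 0.18.

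**Range when every removed patient is a failure.** For true rates of 50% to 70%, 15 v 5 removed gives a gap of 6.2 to 8.7 points and a false-positive chance of 13% to 28%. The more extreme 15 v 0 gives 8.8 to 12.4 points and 22% to 50%. Equal removal, 15 v 15, gives 60/85 in both arms and no gap. Exchanging the arms reverses the sign.

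**The case against.** The strongest objection is that no section defines the analysis population. A withdrawal list says when patients leave, and 100 reduced to 85 is ordinary attrition arithmetic. Analysis sets and missing-data rules commonly sit in a fuller protocol or SAP, which is not shown. This stands in part: a reader might infer that the plan prescribes a completers-only analysis, but that is inference and not stated. The point does not rest on silence alone, however. The article itself labels these as rejection criteria, links one of them to statistical analysis, withdraws deteriorating patients from the trial, and takes those left as the final sample. If follow-up ends at withdrawal, later wording in a SAP cannot recover the missing day-28 data.

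Three further readings are tempting and are not supported:

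- **That the bias favours the decoction.** If the decoction works, more control patients may be withdrawn for deterioration, which would bias against it. Criteria 3 and 7 refer to the regimen and to compliance in general, and both arms receive standard therapy, so neither is confined to the decoction arm.
- **That deaths count as drop-outs and vanish.** Criterion 6 concerns patients who withdraw. The Secondary outcomes section compares day-28 mortality and counts survival days for those who die, so deaths are kept as data. Only a death after an earlier withdrawal could be lost.
- **That the trial is stated to be open-label.** The Randomization section mentions coded packaging and unblinding. No placebo is described, so knowledge of the arm is likely, but the text is not consistent on this.

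It is also fair that poor compliance, co-medication, incomplete data or a patient's own decision need not mean failure. The table shows how quickly the gap shrinks as f falls.

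**Conclusion.** The concern holds in this form: the withdrawal rules and the sample-size text, read together, imply that some treatment failures leave the primary comparison, partly at the investigator's discretion. Sign and size are unknown. Under the assumed 60% rate and 15 v 5 split, the spurious gap runs from 0 to about 7.4 points and type I error from 5% to about 18%, depending on how many of those removed are failures. The response rate, the split, the failure fraction and the yes/no endpoint are all assumptions; the documents supply only the 100, the 15% limit and the 85. It would be too strong to say that the randomised comparison is destroyed, since a possible bias of unknown direction does not show that. Because it touches the primary outcome and can be prevented only while follow-up is still possible, it should be corrected in the protocol and not left to analysis wording.

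**What to change.** 1. Separate stopping study treatment from leaving the study, and drop rejection as a consequence of deterioration, reactions, co-medication, compliance or incomplete data.
2. Make the primary analysis one of every randomised patient in the assigned arm.
3. Record the day-28 grade and vital status for withdrawn patients who still consent.
4. Count death and withdrawal for deterioration as lack of efficacy in the primary outcome.
5. State a missing-data method for other missing grades.
6. Keep the per-protocol analysis as a sensitivity analysis only.
7. Reword the Sample size section so that 100 per arm are analysed, with 85 described as the expected minimum number completing.

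The cost is protocol wording, a day-28 record check or status enquiry for withdrawn patients, and stated response rates that will look less favourable. No change to the clinical rules for stopping treatment is proposed.

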### Ethics

This trial is conducted in accordance with the *Helsinki Declaration* and Chinese Good Clinical Practice and relevant regulations and has been approved by the Medical Ethics Committee of Longhua Hospital Shanghai University of Traditional Chinese Medicine. To protect the privacy of subjects, data processing is performed anonymously and written informed consent is obtained from each patient before initiation of the clinical trial.

### Randomization and allocation

In each study site, patients with MDRO HAP that fulfill the inclusion criteria and do not meet any of the exclusion criteria are assigned to the trial group or control group according to the corresponding random numbers extracted in the order at visit. Each study site will enroll 40 patients for a total of 200 over the five study sites. A random number table generated using Statistical Analysis Software (SAS), version 9.2, using the randomization method, will be used to assign the participants in a ratio of 1:1, with 100 patients each in the trial group and control group. A researcher will generate the allocation sequence and enroll participants and the clinical researchers will assign participants to interventions. The clinical researchers at each center will provide packaged drugs to the participants according to the randomization number on the packaging; the code labeling will conform to the principles of GCP. The statistician will uncover the blinding as necessary.

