### Interventions

The treatment course is 28 days.

The control group will be given standard Western medicine therapy, including: routine monitoring of vital signs; blood, arterial blood gas, and biochemical analysis; coagulation monitoring; step-down antimicrobial therapy; handle the respiratory secretions; mechanical ventilation; liquid nutrient support; maintenance of blood sugar, acid base, and electrolyte balance; correct coagulation function; etc.

The trial group will receive standard Western medicine therapy plus *Buzhong Yiqi* decoction (*Radix Astragali seu Hedysari* 45 g, *Radix Codonopsis* 15 g, fried *Rhizoma Atractylodis Macrocephalae* 15 g, prepared *Radix Glycyrrhiza* 15 g, *Radix Angelicae Sinensis* 10 g, *Pericarpium Citri Reticulatae* 9 g, *Rhizoma Cimicifugae* 12 g, and *Radix Bupleuri* 20 g; NONG’s granular preparation, dissolved in 200 mL warm boiled water and taken orally or by nasal feed once daily).

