### Data collection and management

Data will be managed using the electronic data capture (EDC) system. The study protocol and case report form (CRF)-related materials are provided by the research team to a professional institution for clinical data management and study data statistics, which will establish an electronic case report form (eCRF) for the team, set up a personalized database for data recording, and is responsible for management of the study site’s EDC system. The Standard Protocol Items: Recommendations for Interventional Trials (SPIRIT) flowchart of the trial is shown in Fig. 2.

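### The researcher who generates the allocation sequence also enrols patients, and the protocol mentions unblinding although patients and treating staff cannot be blinded

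*Protocol article*

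**What the plan says.** Two statements in Randomization and allocation matter here.

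- **Who does what.** "A researcher will generate the allocation sequence and enroll participants and the clinical researchers will assign participants to interventions". Patients go to an arm "according to the corresponding random numbers extracted in the order at visit".
- **Packs and blinding.** "The clinical researchers at each center will provide packaged drugs to the participants according to the randomization number on the packaging". Code labelling is to follow GCP, and then "The statistician will uncover the blinding as necessary".

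The Interventions section describes the arms. "The control group will be given standard Western medicine therapy", and "The trial group will receive standard Western medicine therapy plus *Buzhong Yiqi* decoction". Only the second arm has a study product, and no placebo or dummy granules appear anywhere in the article.

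The primary outcome is a four-grade TCM efficacy rating. It combines symptoms, signs, in three of the four grades examination results, and cut-offs of 90%, 60% and 30% on a syndrome efficacy rate. The article does not say who assigns the grade. The only separation of roles it states is under Data analysis, where the statistical analysts are kept out of clinical observation.

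**The concern.** There are two separate problems.

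**Concealment (knowledge before assignment).** Whoever generated the list and also enrols can know which arm the next patient will get. Without any conscious intent, that person can bring a patient forward, defer one, or read a borderline eligibility criterion differently depending on the coming arm. Prognosis then differs between arms at baseline. Adjustment corrects only for the factors that were measured, so the loss cannot be reliably repaired afterwards.

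**Blinding (knowledge after assignment).** The unblinding sentence tells the reader that a blind exists. With an add-on treatment and no placebo, patients and treating staff know the arm. A reader who believes in the blind will give the symptom-and-sign part of the primary outcome more weight than an open-label comparison deserves.

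**Working it through.** The point rests on the text, so the main check is to set the statements side by side.

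**1. Role overlap.** Sequence generation and enrolment are both given to the same researcher. Clinical researchers carry out the assignment afterwards, but a separate assigner does not protect concealment if the person choosing whom to enrol has already seen the list. Taking numbers in order of visit makes the next number predictable to anyone holding it. The article names no barrier such as central release or sealed envelopes. A fuller protocol could add detail, but to cure this it would have to contradict the sentence as printed.

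**2. Blinding against interventions.**

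| Statement in Randomization and allocation | Arms under Interventions | Consequence |
|---|---|---|
| Numbered packs are handed to participants | Only the trial arm has a study product | Having a pack reveals the arm |
| The statistician uncovers the blinding | Control gets standard therapy, no placebo | Patients and treating staff have no blind to uncover |

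The two sections cannot both be read literally unless the blind refers to somebody else, such as the analysts or an outcome grader. The article does not say so.

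**3. The plan's own figures.** 5 sites × 40 = 200 = 2 × 100. Allowing for withdrawal, 85 / (1 − 0.15) = 100 per arm. Both reproduce and neither is in dispute. The article gives no effect size or power, so it contains nothing from which the bias could be sized.

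**4. Illustration of the stakes (assumed inputs).** Suppose the grade is reduced to responder or non-responder, the true response p is equal in both arms at 50–70%, n = 85 per arm, and the test is two-sided at 0.05 (the article gives 0.05 but not the sidedness). Let selection or grading create a spurious gap b. With p1 = p, p2 = p + b and p̄ = (p1 + p2)/2:

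- se0 = √[2 p̄(1 − p̄)/n]
- se1 = √{[p1(1 − p1) + p2(1 − p2)]/n}
- c = 1.96 × se0
- P(reject) = Φ[(b − c)/se1] + Φ[(−b − c)/se1]

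For p = 0.60 and b = 0.10: p̄ = 0.65, se0 = 0.0732, c = 0.1434, se1 = 0.0728. P(reject) = Φ(−0.597) + Φ(−3.35) ≈ 0.276.

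| Spurious gap b | p = 0.50 | p = 0.60 | p = 0.70 |
|---|---|---|---|
| 0 | 5.0% | 5.0% | 5.0% |
| 5 points | 10.0% | 10.3% | 11.3% |
| 10 points | 25.7% | 27.6% | 32.4% |
| 15 points | 50.7% | 55.2% | 65.1% |

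The table shows how sensitive a trial of this size is to a modest bias. It does not estimate the bias this trial will have.

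**The case against.** The best defence is that this is a condensed article. Assessor masking, envelopes or central release may be described in the full protocol, and silence on them is not an error. That is correct, and it limits the point in several places. A reader might infer more than the article supports:

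- **That allocation is unconcealed because control has no placebo.** This does not follow. An open-label add-on trial can have fully concealed allocation through central assignment. Lack of a placebo defeats blinding of patients and treating staff, and concealment by packs. The concealment problem rests on the role overlap.
- **That the primary outcome is graded by staff who know the arm.** The article does not say who grades it. A masked grader is possible, although symptoms reported by patients would still be open-label.
- **That the outcome is wholly subjective.** Three of the four grades also use examination results, and all four carry numeric cut-offs.
- **That all 200 allocations are foreseeable.** This is a worst case. It needs the same researcher to enrol at every site and to keep the list to hand, and the article states neither.
- **That the packs are a failed concealment device.** The article never says they are meant to conceal. They may simply be product labelling for the trial arm.

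The defence does not reach the two explicit statements: that one researcher generates the sequence and enrols, and that there is a blind to uncover.

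**Conclusion.** The concern holds in two parts. First, as written, allocation is not concealed from the researcher who generates the sequence and enrols patients, which opens the trial to selection bias. Second, the blind implied by the unblinding sentence cannot exist for patients and treating staff under the arms described, and the two sections must be reconciled. Both parts come from stated text and need no assumption about what the article omits.

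The size of any resulting bias cannot be derived from the document. Under the assumptions above, a spurious gap of 5 to 10 points would lift the false-positive rate from 5% to between about 10% and 32%. Whether the grading of the primary outcome is itself biased remains open, because the grader is not identified. The sample-size arithmetic is unaffected. The role overlap should be corrected in the plan, because its effect cannot be reliably undone in the analysis.

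**What to change.** **Separate the roles.** Have someone with no part in enrolment generate and hold the sequence by site. This could be the trial statistician or the body described under Data collection and management as "a professional institution for clinical data management and study data statistics". The Data analysis section puts the lead hospital in charge of data management and statistics, so the text should name which body holds the list. Release each allocation, for example through the existing EDC system, only after consent and eligibility are recorded. Bar anyone with access to the list from enrolling.

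**Correct the blinding text.** State that the trial is open-label for patients and treating staff. Then either remove the unblinding sentence or say exactly who is blinded, for example the analysts, or an outcome grader from existing staff who is not told the arm. Keep the pack labelling only as labelling of the trial-arm product.

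**Interpretation.** Present the TCM grade as an open-label result, beside 28-day mortality and pathogen clearance, which are already listed as secondary outcomes.

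**Cost.** One allocation step in the EDC system, some protocol wording, and an open acknowledgement that the trial is open-label. No extra patients or visits are needed.
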